## 8.2 Secondary endpoints

**8.2.1** Intervention: Proportion of HIV test completion 4 weeks after clinic visit

**8.2.2** Implementation Strategy: cost-effectiveness, return on investment (ROI), budget impact, number clinics that complete assessments as intended

## 8.3 Sample Size Estimate and Power.

A priori sample size calculation for the three-arm RCT was based on the expected annual patient volume across six clinics of approximately 7,800. We make the conservative assumption that 5-10% of these will score medium/high-risk on the Gyn HIV Risk Tool based on our preliminary studies, yielding 390 patients annually, with a total of 1,170 over three years of enrollment. Our estimate is conservative as we found that close to 70% of patients in one of our clinics scored medium/high, but these were adolescents and young adult women who have the highest prevalence of STIs and risk behaviors. These 1,170 patients will be seen by an expected 42 providers, where providers will be randomized to receive the potential intervention along with their patients. Given that patients using the same provider are not likely to be strongly related to each other in their choices for PrEP uptake (our co-primary outcome), we assume a low intra-provider correlation (IPC) of 0.01, with on average 28 patients per provider per year, yielding a design effect of  $1 + (28 - 1) * IPC = 1.27$ . Given these assumptions, if we estimate PrEP uptake at 6% (prelim data), we will be able to detect a difference of 9% (from 6 to 15%) between arms with 80% power. We will examine the intervention effect within specific race/ethnicity groups. We will include race and ethnicity in our minimizing of differences between arms at randomization, so we can assume that race and ethnicity will be similarly distributed across arms. Assuming we have approximately 50% non-Latinx Black patient participants (as we do for the general patient population), we expect to enroll 585 non-Latinx Black patients, allowing for 80% power to detect a difference of 6% in PrEP uptake in the standard of care arm to 15% in the intervention arms, assuming the same design effect of 1.27.

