## 5. STUDY POPULATION

### 5.1 Selection of the Study Population

**Provider eligibility:** N=42 ObGyn providers will be randomized. We chose providers as the unit of randomization to minimize contamination of the arms as many providers see patients at more than one clinic site. This will reduce the provider from being exposed to both interventions and unconsciously applying them to patients in the control arm.

**Patient eligibility:** Cisgender women of the enrolled providers aged 15-65 years scheduled in Epic for one of the following visit types: well-woman exam (annual exam), STI testing, pre-conception counseling, or contraception consult (birth control) will complete the eSHxForm. Programming in Epic will assign each patient to a study arm based on their provider's assigned study group. The age range was selected based on the United States Preventive Services Task Force (USPSTF) HIV Testing Recommendations, and PrEP FDA-approved age of 15 years. Based on preliminary clinical data, we estimate that we will have 23,400 women who will complete the eSHxForm and an estimated 5% (n=1170) will fulfill eligibility for PrEP.

**Staff eligibility:** N= 50 clinical staff who work at one of the six Obgyn clinics. These will include front desk, medical assistants, nurses, and clinic managers.

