## 8.5 Quantitative Analyses.

We will examine whether study randomization to the three intervention arms resulted in similar provider and patient groups by comparing patient and provider level demographics with descriptive statistics. Comparison of the primary outcome between arms will be conducted based on provider arm assignment, in accordance with intention to treat. We will use generalized linear mixed-effect models with logistic regression to examine the difference in PrEP uptake (primary outcome) across arms. To account for the relationship among primary outcomes for patients with the same provider, we will specify a random provider effect. In addition, because some patients may return over the study period and be assisted by a different provider than their initial visit, we will specify a random effect for each patient, and assume a joint multivariate normal distribution for these provider and patient random effects. We will adjust these comparisons for any demographic differences

observed between arms. We will examine the primary outcome stratified by race/ethnicity. In exploratory analyses, we will examine whether intervention effects attenuate over time, as providers and patients may become accustomed to the intervention. **Secondary Outcomes:** Similar to our methods for comparing the primary outcome between provider arms, we will also compare the rate of male partner HIV self-test completion (confirmed via text message or phone/video call) with generalized linear mixed-effect models with a provider and patient level random effects. We will use similar methods to compare the HIV test completion rates of male partner and patients who score low-risk. We will consider adjustment for factors that are imbalanced between arms in these analyses. In addition, we will also examine PrEP uptake among low-risk score patients to determine whether providers who are receiving the intervention are being influenced in their behavior more generally, or if the intervention effect is specific only to intervention patients. R (ver 4.1) will be used for analyses.

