### **12.2 Data Integrity**

Implementation of the clinical trial will be studied alongside effectiveness of the interventions. Every 6 months, the research team will review and analyze outcome data and processes via focus group discussions with clinic staff, field notes, and RedCap data analyses. Focus group discussions will occur during routinely scheduled staff meetings to identify barriers and facilitators to the research (see Table 1 above for RE-AIM framework to guide the discussions). Field notes will be taken by a research coordinator/assistant who will observe the implementation of the study at the clinic and take notes about the workflow, patients' questions, and providers' and stakeholders' concerns. Additionally, the proportion of consecutive eligible patients who complete the eSHxForm will be assessed per clinic. If completion is <75%, then research staff will obtain immediate feedback from clinical staff about barriers to completion and devise a plan to increase completion.

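### Three years of clinic volume (23,400) is carried forward unchanged as women who complete the form, and 5% of it as 1,170 eligible women, with no allowance for non-completion or returning patients

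*Protocol*

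**What the plan says.** Protocol section 8.3 builds the sample size on an "expected annual patient volume across six clinics of approximately 7,800". It then applies a risk share: "We make the conservative assumption that 5-10% of these will score medium/high-risk on the Gyn HIV Risk Tool". The lower end, 5%, gives 390 a year, "with a total of 1,170 over three years of enrollment".

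Section 5.1 turns the same volume into completed forms: "we estimate that we will have 23,400 women who will complete the eSHxForm", of whom "an estimated 5% (n=1170) will fulfill eligibility for PrEP". The protocol summary repeats 23,400 as the patient sample size. Section 8.3 halves 1,170 to get 585 non-Latinx Black patients and claims 80% power for 6% versus 15% both overall and in that subgroup.

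Other sections bear on how many forms and women to expect:

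- Section 5.3 excludes women who are unable or unwilling to complete the form. Section 6.1 drops those who cannot finish it even with staff help.
- Section 8.1.2 makes the proportion completing the form a primary implementation endpoint.
- Section 12.2 (and 7.4.1) sets a trigger for action: "If completion is <75%, then research staff will obtain immediate feedback from clinical staff".
- Section 8.5 expects returns: "some patients may return over the study period and be assisted by a different provider than their initial visit". Under sections 5.1 and 5.2 an annual exam is a qualifying visit, and enrolment lasts three years.

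**The concern.** A volume figure and a count of unique women with a completed form are different quantities. They coincide only if every patient completes the form and no patient is counted in more than one year. The protocol says neither will hold exactly, and it sets out to measure the completion proportion that its sample size silently fixes at 1. A woman who attends yearly for a well-woman exam could enter the three-year sum up to three times.

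At stake are the enrolment figures in the summary, 5.1 and 8.3, and the power statements derived from 1,170 and 585. The design effect in 8.3 covers clustering by provider only. If some of the 1,170 are repeat visits, correlation within a patient is not allowed for in the sample size, although the analysis model in 8.5 includes a patient random effect.

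**Working it through.** **1. Reproducing the stated figures.** 7,800 × 3 = 23,400. 7,800 × 0.05 = 390; 390 × 3 = 1,170. So 23,400 / (3 × 7,800) = 1.000 and 1,170 / (0.05 × 23,400) = 1.000. The completion factor is 1 and nothing is deducted for returning women.

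**2. What the document supports for completion.** Section 6.1 reports an earlier clinic project: about 65% completed before the visit, the rest were asked to use tablets, and under 5% could not finish unaided. That points to about 95%. Assisted completion could raise it, and unwilling women, for whom no figure is given, would lower it. The 75% in 7.4.1 and 12.2 is an action threshold, so it serves only as a stress test. No repeat-visit rate is given; 20% below is an assumption.

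**3. Counts at a 5% risk share.**

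- 95% completion: 23,400 × 0.95 = 22,230 forms; × 0.05 = 1,111.5, about 1,112 eligible; half, about 556, in the subgroup.
- Stress test, 75%: 17,550 forms; 877.5, about 878 eligible; about 439 in the subgroup.
- Stress test, 75% and 20% repeats: 23,400 × 0.75 × 0.80 = 14,040; 702 eligible; 351 in the subgroup.

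At a 10% risk share these eligible counts double, to 2,223, 1,755 and 1,404.

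**4. Power for 6% versus 15%.** Two-sided alpha 0.05 is assumed, since 8.3 states none. The effective number per arm is n = N / 3 / 1.27. With p̄ the average rate, SE0 = √[p̄(1 − p̄)(1/n1 + 1/n2)] and SE1 = √[p1(1 − p1)/n1 + p2(1 − p2)/n2], power = Φ[(0.09 − 1.96 × SE0) / SE1].

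Example at N = 1,170: n = 307.1 per arm, p̄ = 0.105, SE0 = 0.02474, SE1 = 0.02447; (0.09 − 0.04849) / 0.02447 = 1.696, so power is 95.5%.

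| Scenario (5% risk share) | Eligible | Overall power, pairwise | Subgroup | Subgroup power, pairwise | Subgroup power, two intervention arms pooled |
|---|---|---|---|---|---|
| As stated | 1,170 | 95.5% | 585 | 73% | 83% |
| 95% completion | 1,112 | 94.6% | 556 | 71% | 81% |
| Stress: 75% | 878 | 88.6% | 439 | 61% | 70% |
| Stress: 75% and 20% repeats | 702 | 80.7% | 351 | 51% | 60% |

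All entries use the stated design effect of 1.27. Pooling sets N/3 controls against 2N/3 intervention patients. With the subgroup's own cluster size (585 / 42 = 13.9, design effect 1 + 12.9 × 0.01 = 1.13 at the planned size), pairwise subgroup power is 78%, 76%, 67% and 58% down the rows.

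**5. Break-even.** Overall pairwise power reaches 80% at a total of about 690, which is 690 / 1,170 = 59% of the stated number.

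**6. Possible offset.** The risk share that restores 1,170 is 5% / 0.95 = 5.3% at 95% completion, 5% / 0.75 = 6.7% at 75%, and 5% / (0.75 × 0.80) = 8.3% at 75% with 20% repeats. All lie within the stated 5–10%.

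**The case against.** The best defence is that the inputs are rough and leave room. The volume is approximate, the risk share is taken at the low end of its range, and 13.5.2.1 aims for close to full participation. Section 5.1 rests the 23,400 on preliminary clinical data, so 7,800 may already be limited to eligible visits with enrolled providers. Three years may not be a hard limit either: the study runs five years, and Table 1 places the maintenance phase after the sample size is reached.

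Much of this stands. The document does not say whether 7,800 is gross or net, so a loss from unenrolled providers or other exclusions cannot be shown. The risk range could absorb the losses, although 8.3 does not present it as an allowance for non-completion or returns. An aim of close to 100% is still not 100%. If 7,800 is already net of these losses, one sentence saying so would settle the point.

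Three stronger readings are tempting and are not supported:

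- *The trial expects 75% completion.* That figure is a per-clinic trigger; section 6.1 points much higher.
- *Non-completion is what breaks the subgroup claim.* Pairwise power is already 73% (78% at its own cluster size) at 585, before any loss. Section 8.3 refers to intervention arms in the plural, and if they are pooled the claim holds at 95% completion.
- *The 1,170 are treated as independent.* Section 8.3 applies a provider design effect. Removing repeat visits altogether is also severe, since the endpoint is tied to a visit and the model allows repeated visits.

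**Conclusion.** The inconsistency is real: a volume figure is relabelled as unique women with a completed form, against the protocol's own exclusions, expected returns and completion endpoint. On the document's own completion experience the correction is small: about 1,170 fewer forms (23,400 − 22,230), 58 fewer eligible women and 29 fewer in the subgroup. The deduction for returning women cannot be sized from the document.

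The main comparison is not in jeopardy. Overall power stays above 80% in each scenario shown, including the combined stress test. The subgroup statement is fragile, but part of its shortfall predates any non-completion, and whether it falls short at 95% completion depends on whether the comparison is pairwise or pooled, which 8.3 leaves unclear. These results assume two-sided alpha 0.05 without adjustment for multiple comparisons, equal thirds per arm, an intra-provider correlation of 0.01 and a 50% subgroup share. Severity is minor to moderate.

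**What to change.** In sections 5.1 and 8.3 and the summary:

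1. State what 7,800 counts: women or visits, and all clinic patients or only eligible patients of enrolled providers.
2. Restate expected completers, eligible women and non-Latinx Black women as unique women, after a stated completion rate and first-visit share. About 95% is the document-based completion figure (about 22,230, 1,112 and 556 before any deduction for returns).
3. Show 75% completion and an assumed repeat share, for example 20%, as labelled stress tests, beside the 5–10% risk range that could offset them.
4. Give overall and subgroup power for each scenario, with the alpha and design effect used, and say whether the subgroup's 80% refers to a pairwise comparison or to both intervention arms pooled against control.
5. If repeat visits are meant to count towards 1,170, say so and allow for within-patient correlation in the sample size.

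The cost is restated figures only: no extra patients and no design change. The stated enrolment, and the subgroup power on a pairwise reading, become less favourable.

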## 8.4 Randomization and Blinding

ObGyn providers will be randomly assigned to one of three study arms based on minimization techniques developed by Pocock and Simon. This minimization approach reduces covariate imbalances by utilizing non-uniform assignment probabilities for the different arms. The study arms will be balanced over the different clinics with equal sampling rates. Providers will be randomized in equal proportions between arms (14 providers per arm). All study personnel, study analysts, and patients will be masked to group assignment. Providers will be unmasked to group assignment. New providers who join a practice after another provider has left will undergo randomization.

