## **8.6 Other statistical considerations.**

There is potential for significant interaction between interventions, determinants (for example, patient and provider characteristics), mechanisms (for example, motivation and skills), PrEP outcomes, and that these potential interactions likely have value for practice. It is possible that the intervention may be efficacious for some patients or providers, while not for others. In addition to our primary analysis, we will also examine who is most likely to use PrEP, since the determinants of PrEP uptake are not well-studied in this population, and whether the intervention was more effective for specific groups, focusing on differences by geographic area (zip code), patient marital status, patient insurance type, patient race and ethnicity, patient age, and patient risk score (medium vs high).

We expect differences in the rate of PrEP uptake for different providers that may depend on provider characteristics such as training or type of provider (e.g., nurse practitioner, physician), years in practice, and whether they are of the same race or gender as patients. We do not expect provider characteristics to impact trial outcomes because providers will be randomized to the intervention. However, we plan to examine the impact of provider characteristics on PrEP uptake independent of the intervention in secondary analysis, using generalized linear mixed-effect models, analogous to methods used in our primary analysis.

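### Section 8.3 gives 80% power for 6% vs 15% at both 1,170 and 585 patients with one design effect; pairwise, its inputs give about 95% and 73%

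*Protocol*

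**What the plan says.** Protocol 8.3 builds the sample from clinic volume, "yielding 390 patients annually, with a total of 1,170 over three years of enrollment". It goes on: "These 1,170 patients will be seen by an expected 42 providers". Section 8.4 divides these providers equally, 14 to each of three arms. With an intra-provider correlation (IPC) of 0.01 and a cluster size given as "with on average 28 patients per provider per year", section 8.3 obtains a design effect of 1 + (28 - 1) × 0.01 = 1.27.

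Two power statements follow. For the full sample: "we will be able to detect a difference of 9% (from 6 to 15%) between arms with 80% power". For the subgroup, taken as half the patients, "we expect to enroll 585 non-Latinx Black patients", and the claim is 80% power to "detect a difference of 6% in PrEP uptake in the standard of care arm to 15% in the intervention arms". The protocol says explicitly that the design effect of 1.27 is carried over. Section 8.3 states neither the significance level nor whether the test is one- or two-sided.

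**The concern.** The two statements share the control rate, the target rate, the power and the design effect. Only the sample size differs, and it differs by a factor of two. With one test at one level, halving the sample must lower the power or widen the detectable difference, so at least one statement cannot be the power at 6% vs 15%.

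The cluster size is a second slip in the same calculation. The 28 comes from dividing the three-year total by the number of providers, but it is labelled as yearly.

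This paragraph is the protocol's power justification. A reader cannot tell from it how much room the main comparison has. A reader of the race-stratified analysis planned in 8.5 may also take a null subgroup result to carry more weight than it does.

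**Working it through.** **Inputs (8.3 and 8.4).** 1,170 patients in three equal arms: 390 per arm. Subgroup of 585: 195 per arm. 42 providers. IPC 0.01. Rates 6% and 15%. Assumed, because not stated: two-sided 5%, pairwise comparison, no dropout.

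**Cluster size.**
- Three years: 1,170/42 = 27.9. Per year: 390/42 = 9.3.
- Subgroup over three years: 585/42 = 13.9.
- The protocol's 1.27 reproduces with 28 as the three-year figure: 1 + 27 × 0.01 = 1.27.
- Read literally as yearly, it would mean 84 patients per provider, 42 × 84 = 3,528 patients and a design effect of 1 + 83 × 0.01 = 1.83. None of these matches the rest of 8.3.

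**Formula.** Two-proportion z-test with pooled variance under the null and n effective patients per arm (patients divided by design effect):

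power = Φ{[0.09√n − 1.96√(2 × 0.105 × 0.895)] / √(0.06 × 0.94 + 0.15 × 0.85)} = Φ{[0.09√n − 0.850] / 0.429}

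**Pairwise results.**

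| Sample | Design effect | Effective n per arm | Power, 6% vs 15% | Rate detectable against 6% at 80% power |
|---|---|---|---|---|
| 1,170 | 1.27 | 390/1.27 = 307.1 | 95.5% | about 12.5% |
| 585 | 1.27 | 195/1.27 = 153.5 | 73.2% | about 16.0% |
| 585 | 1 + 13 × 0.01 = 1.13 | 195/1.13 = 172.6 | 78.1% | about 15.3% |

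The stated 80% is not reproduced in any row. Working backwards, 80% needs 181 effective patients per arm. At 1.27 that is 181 × 1.27 = 230 per arm, or about 690 in three arms, which lies between 585 and 1,170. With 195 per arm, 80% needs a design effect of at most 195/181 = 1.08.

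**Other tests, pairwise, design effect 1.27.**

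| Variant | 1,170 | 585 |
|---|---|---|
| Unpooled variance | 95.7% | 73.9% |
| Arcsine | 96.1% | 74.9% |
| Continuity-corrected | 94.1% | 66.7% |
| t with 26 df | 94.3% | 70.7% |
| One-sided 5% | 97.8% | 82.6% |
| Two-sided 1.67% (three pairs) | 89.6% | 57.2% |
| Two-sided 1% | 85.9% | 49.9% |

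Solving the formula for the level that gives exactly 80%:
- Full sample: z = (0.09√307.1 − 0.8416 × 0.4288)/0.4335 = 2.81, a two-sided level of about 0.005.
- Subgroup: z = (0.09√153.5 − 0.8416 × 0.4288)/0.4335 = 1.74, a two-sided level of about 0.08.

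No single level gives 80% for both.

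**Both intervention arms pooled against control (1:2).** At 1.27 the subgroup has 83.3% (78.6% with continuity correction) and the full sample 98.9% (98.5%). At 1.13 the subgroup has 87.7%.

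**The case against.** **The full-sample error is harmless.** This stands as to consequence. The inputs support more than 80%, so neither the planned number nor the design is threatened. Read as a floor, the full-sample statement is even true. It is still not the power at 6% vs 15%.

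**The subgroup sentence speaks of intervention arms in the plural.** This stands in part. If both are pooled against control, about 83% at 1.27 supports the subgroup claim, and a one-sided 5% level would also do so pairwise. A reader might infer that the subgroup claim is certainly overstated. The document does not support that, because it names neither the comparison nor the level. Neither reading gives 80% in both samples, however: the full sample is then about 99% or 98%. The full-sample sentence refers to a difference between arms, and objective 3.1.1 contrasts the two interventions, which a pooled comparison does not address.

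**Reusing 1.27 is conservative.** True: the subgroup has fewer patients per provider. At 1.13 the pairwise shortfall is about 2 percentage points. That figure assumes an even spread of Black patients over 42 providers, which the protocol does not state.

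**The IPC.** A reader might infer that 0.01 is contradicted by 8.6, which says "We expect differences in the rate of PrEP uptake for different providers that may depend on provider characteristics", or that the trial is therefore underpowered. The document does not support this. Section 8.6 gives no size for those differences, an IPC of 0.01 already allows for some, 8.5 fits a random provider effect, and 8.6 adds that randomisation should keep provider characteristics from affecting the outcome. Any larger IPC would be the reader's own choice.

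**Conclusion.** The two 80% statements cannot both be the power at 6% vs 15%. This follows from 8.3 alone and does not depend on the choice of test or level.

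The size does depend on assumptions. At two-sided 5% and pairwise, the full sample is understated by about 15 points, in the safe direction. The subgroup is overstated by about 7 points at 1.27 or about 2 points at 1.13. With the intervention arms pooled, the subgroup claim is met and only the full-sample figure is off.

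The yearly label on the cluster size is wrong on the protocol's own numbers. The design effect of 1.27 is right for the full sample once 28 is read as a three-year figure. These are misstated figures in the power justification. They do not show that the primary comparison is too small.

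**What to change.** Restate 8.3 so that it:

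- names the significance level, its sidedness, and the comparison (pairwise, or intervention arms pooled against control), the same for both statements;
- gives the cluster size as about 28 patients per provider over three years;
- gives full-sample power as about 95% for 6% vs 15%, or 80% for 6% vs 12.5%;
- gives pairwise subgroup power as about 73% at design effect 1.27, or about 78% at 1.13 with the even-spread assumption stated. If pooling is intended, say so and give about 83% and 88%, with about 99% for the full sample.

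These figures are for two-sided 5% and must be recomputed if another level is meant.

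Optionally, show power at larger IPC values. For example, the pairwise full-sample power stays at or above 80% up to a design effect of 390/181 = 2.155, an IPC of (2.155 − 1)/27 = 0.043. This would be an addition, not the correction of an error.

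The cost is protocol wording only, with no change to sample size, arms or analysis. The downside is a slightly less favourable pairwise power for the subgroup.
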